**5.1.1 Description**

The hypothesis will be tested in children with tetralogy of Fallot undergoing elective open heart surgery with standard heart arrest and cardiopulmonary bypass. An informed consent will be obtained from all the patients’ parents or guardians. 40 patients will be recruited in to the study within two years. They will be randomized into 2 equal sized groups: Group I control (Sham, n=20) and Group II preconditioning (RIPC, n=20).

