# SUBJECT ENROLLMENT AND RANDOMISATION

- 1. **Recruitment**

Patients will be recruited by either the surgeon ([name]) or cardiologist ([name]) at the preadmission clinic or on the ward prior to surgery. The clinician ([name]/[name]) will explain to the patient’s parents/guardians, the research project, their child’s role, and outcomes and will obtain signed consent if granted.

- 1. **Eligibility Criteria**
     1. **Inclusion Criteria**

Patients with tetralogy of Fallot aged one month and older (to 18 years) having surgery for the first time.

- - 1. **Exclusion Criteria**

Patients with chromosomal defects, associated congenital lung malformations and haematological disorders will be excluded.

- 1. **Randomisation Procedures**

Random allocation is made in blocks in order to keep the sizes of the 2 treatment groups similar. In order to avoid predictability, the block size that is randomly selected is 2, 4 or 5, as the sample size must be divisible by the block size. Due to the expected relative uniformity of condition in the patient group and the small number of subjects the design will not be stratified. The randomisation will be performed in secret by a member from Heart Research (not involved in working for the trial) using SPSS statistical software generated randomisation and will place each designation sequentially in numbered envelopes 1 to 40, for patient 1 to 40 and the envelopes will be signed and sealed. The implementer of the RIPC or Sham co ntrol treatment protocols will open one envelope in numerical order immediately prior to placement of the blood pressure cuff and they will apply the RIPC treatment or sham control protocol accordingly.

- 1. **Blinding Arrangements**

[name] will not be blinded as she will be applying the RIPC treatment. She will also be involved in randomisation, sample collection, data collection, data entry and laboratory analysis. Surgeons, perfusionists, anaesthetists will be blinded. Samples will be de-identified and therefore, research laboratory staff will be blinded to the patient’s identity. The blood pressure cuff will be positioned on the thigh for both sham control and RIPC groups, however if other theatre staff witness whether the RIPC treatment protocol is invoked they will not be blinded. As these theatre staff are strictly performing standard clinical tasks and procedures and are not involved in the trial and analysis *per se*, this should not impact the blinding.

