# STATISTICAL METHODS

**10.1 Sample Size Estimation**

Sample size is based primarily on the successful study of RIPC in children (see ref 17) where n=approximately 20 per treatment group. This prior study was amply powered to detect differences in clinical and molecular measures. Notably, post-operative inotrope usage was greatly diminished by RIPC. Based on these inotrope usage results, a power of 0.8, alpha=0.05 and sigma of 3.9 indicates that a sample size of n=20 was required. Injury was deemed to be diminished by RIPC on the basis of reduced troponin I release, thus for a power of 0.8, alpha of 0.05 and a sigma of 3 the sample size required is calculated as n=16. Based on our laboratory’s ability to detect a 20% difference in mitochondrial oxygen consumption in human tissue preparations at least 10 subjects are required to detect this difference (power=0.8, sigma=14.5, alpha=0.05, 2 groups. Similarly, the detection of changes in many mitochondrial proteins measured by proteomic assays, are also quite sensitive ranging between 10-20%. Thus a sample size of n=20 per group will yield ample statistical power.

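### A block of 5 cannot be split equally between two arms, so the stated block rule does not assure the planned 20:20 allocation

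*Protocol*

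**What the plan says.** Protocol section 6, under Randomisation Procedures (6.3), gives the purpose of blocking: "Random allocation is made in blocks in order to keep the sizes of the 2 treatment groups similar". It then fixes the sizes and the reason for them: "the block size that is randomly selected is 2, 4 or 5, as the sample size must be divisible by the block size". There is a single list, since "the small number of subjects the design will not be stratified", and the person who generates it "will place each designation sequentially in numbered envelopes 1 to 40, for patient 1 to 40".

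Two other places give the arm sizes that the list should produce. Section 5.1.1 states: "They will be randomized into 2 equal sized groups: Group I control (Sham, n=20) and Group II preconditioning (RIPC, n=20". Section 10.1 concludes: "Thus a sample size of n=20 per group will yield ample statistical power".

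The protocol does not say how a block of 5 is divided between the arms, how likely each block size is, whether one size serves the whole list or sizes are mixed, or how overall balance is restored if blocks are uneven.

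**The concern.** The sizes were chosen by testing whether they divide the total sample size. What keeps two arms equal is that each block is divisible by the number of arms, and 5 fails that test. A list made as section 6.3 describes may therefore not give the equal groups of section 5.1.1 or the n=20 per group of section 10.1.

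Section 6.3 is the working instruction for someone outside the trial team who prepares 40 sealed envelopes. If blocks of 5 occur, that person must either accept that the arms may differ in size or match 3:2 blocks with 2:3 blocks, a step that the protocol does not describe. An auditor could not tell from the text which list was intended.

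**Working it through.** **Inputs.** Total 40 and 20 per arm (sections 4 and 5.1.1); block sizes 2, 4 and 5, one list, 40 envelopes (section 6.3); n=20 per group (section 10.1). Two assumptions are not in the protocol: the three sizes are equally likely, and a block of 5 is 3:2 or 2:3 with probability 1/2 each.

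**Step 1: the plan's own criterion.** 40/2 = 20, 40/4 = 10, 40/5 = 8. All are whole numbers, so the stated divisibility is correct.

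**Step 2: the criterion that matters for two arms.** The remainder on division by 2 is 0 for sizes 2 and 4, and 1 for size 5. A block of 5 is never balanced. This step needs no assumption.

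**Step 3: is 20:20 still attainable?** Suppose complete blocks fill 40 and k of them are 5s. The rest, 40 − 5k, is made of 2s and 4s and must be even, so k is even. Then k/2 blocks of 3:2 and k/2 of 2:3 give 20:20. It is attainable, but with independent composition it is not assured:

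P(20:20 | k) = C(k, k/2) / 2^k

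- k = 0: 1
- k = 2: 2/4 = 0.50
- k = 4: 6/16 = 0.375
- k = 6: 20/64 = 0.3125
- k = 8: 70/256 = 0.273

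At k = 8 each arm has between 8 × 2 = 16 and 8 × 3 = 24 patients, so the extreme for complete blocks is 16:24.

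**Step 4: chance of unequal arms under each reading.**

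- *One size drawn for the whole list.* Only a draw of 5 causes imbalance: (1/3) × (1 − 0.273) = 0.242. The share within 19:21 is 2/3 + (1/3) × (0.273 + 2 × 0.21875) = 0.90.
- *Sizes mixed, list cut at envelope 40.* The exact distribution was built block by block, with a hypergeometric split of any block that is cut. P(20:20) = 0.377, so 62% of lists are unequal. The share within 19:21 is 0.377 + 2 × 0.2435 = 0.864.
- *Sizes mixed but fitted to fill 40 exactly* (each step chooses equally among the sizes that still allow a complete fill). P(20:20) = 0.417, so 58% are unequal. The share within 19:21 is 0.417 + 2 × 0.245 = 0.908.

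**Step 5: effect on power.** Section 10.1 says of inotrope use that "a power of 0.8, alpha=0.05 and sigma of 3.9 indicates that a sample size of n=20 was required". It gives no difference and does not say whether the test is two-sided. Taking n=20 as per group and the test as two-sided, the implied difference by the t test is 3.55, so d = 3.55/3.9 = 0.909. Power then depends on the noncentrality d × √(n₁n₂/40):

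- 20:20: 0.909 × √10 = 2.87, power 0.800
- 19:21: power 0.799
- 18:22: power 0.796
- 17:23: power 0.791
- 16:24: 0.909 × √9.6 = 2.82, power 0.784

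**Step 6: does the fix work?** Four blocks of 4 and four of 6 fill 16 + 24 = 40 places, with 4 × 2 + 4 × 3 = 20 per arm, so 20:20 is certain. Even sizes alone are not enough: sizes 2 and 4 mixed at random and cut at envelope 40 give 20:20 in only 89% of lists (worst split 19:21). The list must also end on a complete block.

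**The case against.** The strongest reply is that section 6.3 promises only similar group sizes, and by that standard the rule works. With sizes mixed and cut at 40, 86% of lists are within 19:21 and 98.9% within 18:22. With one size for the list the figures are 90% and 97.7%. This stands as far as section 6.3's own aim goes. It does not remove the mismatch with sections 5.1.1 and 10.1, which state equal groups of 20, and it does not make divisibility of 40 the right reason for choosing a block size.

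It is also fair to say that the consequence is small. Unequal arms do not bias the comparison, and power hardly moves. Of the sample sizes in section 10.1, only the inotrope calculation asks for 20. Read per group, troponin asks for 16 and mitochondrial oxygen consumption for 10, and an arm of 16 meets both.

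A reader might infer more than the text supports:

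- *That the block rule and equal groups cannot both hold.* Step 3 shows that they can.
- *That pairing 3:2 with 2:3 blocks would break the stated procedure.* Section 6.3 does not say how a block of 5 is made up, and the order of blocks and the order within them could still be random.
- *That about 73% of lists would be unequal.* That figure (1 − 0.273) applies only if every block is a 5. The wording of section 6.3 fits one size drawn for the whole list at least as well as mixing, and on that reading the figure is 24%.
- *That ending the list inside a block is part of this error.* It arises only when sizes are mixed and cut, and it affects even sizes too.

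**Conclusion.** The rule is wrong as written, and the point is minor. Section 6.3 selects block sizes by divisibility of the total when it should require divisibility by the two arms. Including 5 means that the procedure does not assure the 20:20 stated in sections 5.1.1 and 10.1. This conclusion rests on parity alone.

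The size of the problem rests on the two assumptions above and on the reading of the rule: about 24% of lists unequal with one size for the list, and about 62% with sizes mixed and cut at 40. In both cases most unequal lists are 19:21. The power figures further assume a two-sided test with the inotrope n=20 taken per group. With complete blocks the loss is at most 1.6 percentage points (0.800 to 0.784).

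The documents do not support a claim of bias, of a materially underpowered trial, or of equal groups being impossible. What needs correcting is an instruction that gives a wrong reason and does not secure the arm sizes stated elsewhere.

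**What to change.** In section 6.3, delete 5 and allow only even block sizes, in a set of complete blocks that sums to 40 and is placed in random order. Four blocks of 4 and four of 6 is one example; the sizes still vary, which serves the aim of avoiding predictability. Replace the reason given with two requirements: each block is divisible by the number of arms, and the list ends on a complete block. Once sizes are mixed, no single size needs to divide 40; 6 does not, and the example still gives 20:20.

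The cost is one sentence in the protocol and a list generated under the new rule before the first patient is randomised. Sections 5.1.1 and 10.1 then stand as they are.

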# STUDY VISITS AND PROCEDURES SCHEDULE

The subjects are directly studied only during the perioperative period. Blood and myocardial samples are studied upon arrival to the laboratory (mitochondrial studies) or in batches after freezing (proteomic/microscopy studies).

# CLINICAL AND LABORATORY ASSESSMENTS

**8.1 Proteomic Assessment Methodology**

The plasma samples will be analysed as per protocol outlined below in Figure 3: Strategy for proteomic profiling of plasma samples.

**8.1.1. Sample Preparation**

Plasma samples will be depleted of 4 highest abundance proteins (albumin, alpha-antitrypsin, transferring and haptoglobin) that are of little pathological importance, using the ProteoSpin Abundant Serum Protein Depletion Kit (Norgen Biotek) to unmask the presence of lower abundance proteins of interest. The remaining proteins will be precipitated using the acetone precipitation protocol, as specified in the kit. Removal of these proteins increases the sensitivity of detection for proteins of interest. The protein pellets resulting from acetone precipitation will be re-suspended in 50µl DIGE labelling buffer containing 7M urea, 2M thiourea, 4% CHAPS and 30mM Tris, for 3 hours. Protein content of each sample will be quantified using the Bradford assay, using the Protein Assay Dye Reagent Concentrate (Bio-Rad).

**8.1.2. Sample Labelling and 2D-DIGE**

The internal standard consisting of an equal amount of each one of the two samples to be analysed on each gel will be labelled with the Cy2 dye (GE Healthcare), to minimize gel-to-gel variation. For each time-point, 50% samples will be labelled with Cy3 and 50% samples with the Cy5 dye, with the samples then randomized to gels (2 samples per gel).

Sample labelling will be performed according to the recommendations set by GE Healthcare. The Cy2, Cy3 and Cy5 samples for each gel will be pooled and the loading volume adjusted with labelling buffer (specified above) to 100µl prior to loading onto the 1st Dimension IPG Strip. The 24cm, pH3-11 non-linear Immobiline Drystrips (GE Healthcare) will be rehydrated overnight with rehydration buffer (15ul IPG buffer 3-11NL and 3ml DeStreak solution) from GE Healthcare. Isoelectric focusing will be carried out using the Ettan IPGphor3 Isoelectric Focusing system (GE Healthcare). This system includes software that monitors and records parameters for each run, allowing for standardization across runs. The IPG strips will then be conditioned for 15 min in equilibration buffer containing 2%SDS, 50mM Tris-HCl, pH8.8, 6M urea, 30% glycerol, 0.002% bromophenol blue, and 10mg/mL DTT. The strips will then be alkylated for 15 min in equilibration buffer containing 25mg/mL iodoacetamide instead of the DTT and loaded onto 12.5% polyacrylamide gels. Second dimension will be run using the Ettan Dalt 6 system (GE Healthcare), for an average of 4.5 hours, until the bromophenol blue dye-front reaches the edge of the gels.

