**5.1.5 Blood sampling**

The following 5 blood samples (6.5 ml each) will be taken from the arterial line that is routinely placed in all patients: baseline, immediately after discontinuation of CPB, at 6, 12, and 24 hours following discontinuation of CPB. No additional lines or invasive procedures will be performed apart from those that routinely required for heart surgery. From each sample, 1.5 ml will be used for proteomic assays, and 5 ml for the lymphocyte mitochondrial function assays.

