**8.1.4. Gel Data Analysis**

Data obtained from the gels will be quantified using the DeCyder version 6.5 software (GE Healthcare). The Differential In-gel analysis (DIA) will be used to optimize spot detection, with the master gel being assigned automatically to the gels with most spots detected. The Biological Variation Analysis (BVA) module will be used for analysis of each sample according to the corresponding age-group. The filtering parameters will then be set to determine the spots that: had a p-value ≤ 0.05 for the t-test employed to test the variation between age-groups and a >1.5 fold change in abundance between the groups.

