**8.1.5. Spot Excision and Identification**

Proteins of interest (determined by change from baseline) will be excised robotically using the Ettan Spot-picker (GE Healthcare) and identified by tandem mass spectrometry (MS/MS) on an HPLC-Chip ESI-Trap XCT tandem mass spectrometer or LTQ-FT mass spectrometer. Protein identification will be verified with the use of western blots using specific antibodies.

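### A Cy2 standard made only from each gel's own two samples cannot link gels, and under random gel allocation it about halves the unpaired RIPC contrast

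*Protocol*

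**What the plan says.** Protocol section 8.1.2 describes the Cy2 reference as an "internal standard consisting of an equal amount of each one of the two samples to be analysed on each gel", used "to minimize gel-to-gel variation". On dyes it says "For each time-point, 50% samples will be labelled with Cy3 and 50% samples with the Cy5 dye", and on layout "with the samples then randomized to gels (2 samples per gel". It does not require one RIPC and one sham sample on each gel, and it does not say whether both samples on a gel must come from the same time point.

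Section 8.1.4 keeps spots that "had a p-value ≤ 0.05 for the t-test employed to test the variation between age-groups" and that also differ more than 1.5-fold between groups. Section 8.1.5 then selects for identification: "Proteins of interest (determined by change from baseline) will be excised robotically".

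The arms are "Group I control (Sham, n=20) and Group II preconditioning (RIPC, n=20" (section 5.1.1). Blood is drawn at "baseline, immediately after discontinuation of CPB, at 6, 12, and 24 hours following discontinuation of CPB" (section 5.1.5). That makes 40 samples per time point, 5 × 40 = 200 in all, and 100 gels.

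**The concern.** A Cy2 reference makes gels comparable only if it is the same material on every gel. Here each gel has its own reference, and half of it is the sample being measured. For samples A and B on one gel, the standardised abundances are A/((A+B)/2) and B/((A+B)/2). These average 1 whatever the protein does, so each value says only how a sample compares with its chance gel-mate.

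Both selection rules that follow compare values between gels: the group test with its fold filter, and change from baseline. The plasma proteomic response is part of the primary objective (section 3), and section 10.1 presents 20 per group as amply powered with proteomics in view. The risk is missed proteins. Under random gel allocation the t-test keeps its 5% error under the null (4.6% and 5.3% in simulation), but true effects are pulled towards no change.

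**Working it through.** **Inputs from the protocol.** 20 per arm; 5 sampling times; two samples per gel at random; gel-specific Cy2 standard; t-test at 0.05; 1.5-fold filter. The protocol computes no proteomic power, so there is no figure of its own to reproduce on this point. The 8.1.4 groups are taken here as RIPC and sham.

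**1. Size of the RIPC contrast.** Let δ be the true log difference.
- Mixed-arm gel: the standard cancels, so the RIPC value minus the sham value has expectation δ.
- Same-arm gel: both values have the same expectation in either arm, so nothing is contributed to the contrast.
- Probability that a sample's gel-mate is from the other arm: 20/39 = 0.513 within a time point, or 100/199 = 0.503 if all 200 samples are shuffled together.
- Expected unpaired contrast: 0.513 δ or 0.503 δ. Simulation gave 0.51 to 0.53 of δ within a time point.

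**2. Against the 1.5-fold filter.**
- True 1.5-fold appears as 1.5^(20/39) = 1.23-fold.
- True 2-fold appears as 2^(20/39) = 1.43-fold, still below the filter.
- True change needed for an expected 1.5-fold: 1.5^(39/20) = 2.20-fold.

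**3. Change from baseline** (simulated with a common 3-fold change, log 1.099, and a between-arm difference in change of log 2 = 0.693).
- One time point per gel: mean standardised abundance is exactly 1 at every time. The common change of 1.099 shows as 0.000. The between-arm difference shows as 0.353 (0.353/0.693 = 51%), split as about +0.15 in RIPC and a spurious −0.20 in sham.
- Time points mixed on gels: the common change shows as 0.625 (0.625/1.099 = 57%).
- Common pool: the common change shows as 1.100 and the between-arm difference as 0.697.

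**4. Power.** The documents give no proteomic SD. Assumed: between-patient log SD 0.3 to 0.6 and technical log SD 0.1.

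| True change, criterion | Log SD | Common pool | Gel-specific standard |
|---|---|---|---|
| 1.5-fold, p ≤ 0.05 | 0.3 | about 97% | 61–70% |
| 1.5-fold, p ≤ 0.05 | 0.4 | 85% | 50% |
| 1.5-fold, p ≤ 0.05 | 0.6 | 51–55% | 26–29% |
| 2-fold, both filters | 0.3–0.6 | about 92–99% | about 33–38% |

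The ranges within a row come mainly from whether technical noise is also put on the Cy2 channel, and from simulation error. For the two-filter criterion the 2-fold case is shown because a true effect exactly at the cut-off passes only about half the time under any design.

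**5. Pairing arms without changing the standard.** With one RIPC and one sham sample per gel the full effect returns (ratio 0.99 to 1.01). But the two values are then close to +(a−b)/2 and −(a−b)/2 on the log scale, so they are strongly negatively correlated. The true variance of the mean difference is up to twice what an unpaired t-test assumes. Roughly, the effective critical value is 1.96/√2 = 1.386, a two-sided error of about 0.166. Simulation gave 11–16%.

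**The case against.** A reader might infer that this standard removes change from baseline altogether, or wipes out the biological signal. The protocol does not support either. Section 8.1.2 does not fix one time point per gel. With one Cy3 and one Cy5 sample on each gel, single-time-point gels would give the even dye split automatically, so specifying that split by time point arguably hints that gels may mix times. On that reading the common change is attenuated, not removed. Even with one time point per gel, only the part common to both arms vanishes. About half of the RIPC contrast survives, and mixed-arm gels keep the full within-gel difference.

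Other points have weight. Section 8.1 refers to a strategy figure that is not visible in the text at hand, so absence of arm pairing is read from the silence of 8.1.2. Section 8.1.4 names age groups, with no group sizes, so the 20/39 factor applies only once RIPC versus sham is substituted. Section 10.3 also lists two-way ANOVA and covariance analysis. The mitochondrial, kinase and microscopy assays are unaffected.

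What remains is enough. The standard's composition is stated outright and cannot link gels under any layout. None of the analyses in 10.3 includes gel as a factor. A within-gel analysis would remove the bias, but under random allocation only about 20 × 20/39 = 10 of the 20 gels per time point would inform the arm comparison. If arms are in fact paired, the effect is intact and the problem becomes the unpaired test's error rate.

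**Conclusion.** The point holds in a bounded form. The gel-specific standard defeats its stated purpose, because values from different gels share no reference. With random allocation and an unpaired RIPC-versus-sham test on the log scale, the expected contrast is about half the truth (51%, or 50% with all times shuffled). That factor needs only the 20:20 split. The effect on change from baseline depends on a layout rule the protocol leaves open: the common change is lost if gels hold one time point, and attenuated (57% in the case simulated) if they do not. The power figures are illustrative, since they rest on assumed SDs, but the loss is large at every value tried. It should be corrected before any gel is run, because the standard cannot be changed afterwards.

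**What to change.** In section 8.1.2, define one Cy2 standard made by pooling equal aliquots across patients, arms and time points, and load that same standard on every gel. Pooling needs no access to the allocation code. State whether a gel may mix time points, and in 8.1.4 name the groups being compared.

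Optionally, place one RIPC and one sham sample on each gel with dyes balanced within arm. Someone outside the blinded laboratory would have to prepare that gel list. If the gel-specific standard is kept, this pairing becomes necessary, and the analysis must use within-gel contrasts (paired or gel-blocked) in place of the unpaired t-test.

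Cost: a wording change, one pooling step and a small aliquot from each sample, with no extra gels. The real drawback is timing. A pool of all samples means no gel can run until the last patient's 24-hour sample is banked. Section 7 already has proteomic samples frozen and run in batches, so this is workable. The alternative is to fix a large pool from the early patients, covering all five sampling times, and use it throughout.
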